## Abstract

**Background:**

Hysterectomy is the commonest major gynaecological surgery. Although there are many approaches to hysterectomy, which depend on clinical criteria, certain patients may be eligible to be operated in any of the several available approaches. However, most comparative studies on hysterectomy are between two approaches. There is also a relative absence of data on long-term outcomes on quality of life and pelvic organ function. There is no single study which has considered quality of life, pelvic organ function and cost-effectiveness for the three main types of hysterectomy. Therefore, the objective of this study is to provide evidence on the optimal route of hysterectomy in terms of cost-effectiveness by way of a three-armed randomized control study between non-descent vaginal hysterectomy, total laparoscopic hysterectomy and total abdominal hysterectomy.

**Methods:**

A multicentre three-armed randomized control trial is being conducted at the professorial gynaecology unit of the North Colombo Teaching Hospital, Ragama, Sri Lanka and gynaecology unit of the District General Hospital, Mannar, Sri Lanka. The study population is women needing hysterectomy for non-malignant uterine causes. Patients with a uterus > 14 weeks, previous pelvic surgery, those requiring incontinence surgery or pelvic floor surgery, any medical illness which caution/contraindicate laparoscopic surgery and who cannot read and write will be excluded. The main exposure variable is non-descent vaginal hysterectomy and total laparoscopic hysterectomy. The control group will be patients undergoing total abdominal hysterectomy. The primary outcome is time to recover following surgery, which is the earliest time to resume all of the usual activities done prior to surgery. In total, 147 patients (49 per arm) are needed to have 80% power at α-0.01 considering a loss to follow-up of 20% to detect a 7-day difference between the three routes; TLH versus TAH versus NDVH. The economic evaluation will take a societal perspective and will include direct costs in relation to allocation of healthcare resources and indirect costs which are borne by the patient. A micro-costing approach will be adopted to calculate direct costs from the time of presentation to the gynaecology clinic up to 6 months after surgery. Incremental cost-effectiveness ratios (ICER) will be obtained by calculating the incremental costs divided by the incremental effects (time to recover and QALYs gained) for the intervention groups (NDVH and TLH) over the standard care (TAH) group.

**Discussion:**

The cost of the procedure, quality of life and pelvic organ function following the three main routes of hysterectomy are important to clinicians and healthcare providers, both in developed and developing countries.

**Trial registration:**

The study was registered in the Sri Lanka clinical trials registry (SLCTR/2016/020) and the International Clinical Trials Registry Platform (U1111-1194-8422) on 26 July 2016.

**Electronic supplementary material:**

The online version of this article (doi:10.1186/s13063-017-2295-7) contains supplementary material, which is available to authorized users.

## Background

Hysterectomy is the most common major gynaecological surgery, with up to 100,000 procedures performed annually in the United Kingdom [1]. The optimal route of a hysterectomy for a patient will depend on the pathological nature, uterine size, uterine descent, endometriosis and the likelihood of pelvic adhesions and adnexal masses, previous pelvic surgery and the surgeon’s preference. Although there are many methods of doing a hysterectomy the methods in mainstream practice are; total abdominal hysterectomy (TAH), non-descent vaginal hysterectomy (NDVH) and total laparoscopic hysterectomy (TLH). In some instances the best route is obvious; e.g. if the uterus is larger than 20 weeks, a TAH may be the optimal method. While in uterine prolapse, with coexistent cystocele or rectocele, a vaginal hysterectomy and repair may be the best route to deal with all the problems. However, there is a group of patients with benign gynaecological conditions for whom any one of the three main methods can be applied. It is worth finding out what is the most cost-effective method of hysterectomy in this ubiquitous group which includes a significant proportion of women undergoing hysterectomy.

Most comparative studies on hysterectomy are between two approaches; vaginal versus laparoscopic, abdominal versus laparoscopic or vaginal versus abdominal [2–6]. These studies and even systematic reviews are underpowered to detect a difference in major complications such as visceral injuries between the three main methods [2–7]. Although initial studies suggested an increased risk of urinary tract damage in TLH, the risk may not be that high now when the effects of the learning curve of laparoscopy and the evolution of the technique of TLH are considered [8]. Although direct costs appear to be high for TLH, a shorter postoperative hospital stay and lower indirect costs appear to make it more cost-effective compared to the standard TAH [4, 5, 9, 10]. There is evidence to suggest that VH appears to be less costly compared to LH according to the eVALuate trial [11]. However to date, there has been no direct comparison of costs between VH and TAH. Neither has there been any study which has attempted to shed light on the costing of hysterectomy in developing countries, where the emphasis should be on cost-effectiveness. Cost of healthcare interventions is an important aspect to consider in limited-resource settings. Although free public healthcare is available in Sri Lanka, it is important to know the cost incurred due to the huge burden on taxpayers. Therefore, direct health sector-related costs should be explored if cost-effectiveness is the ultimate aim, especially for a low- and middle-income country. Indirect costs incorporating loss of productivity are important, especially when the target population involves the population workforce, to get a wider perspective of costs incurred. Against such a backdrop, an ideal costing study would need to involve a broader societal perspective considering direct costs related to the health sector and indirect costs incorporating recovery-related costs and loss of productivity.

There is also a relative paucity of data on long-term outcomes; quality of life, urinary, bowel and sexual function in randomized controlled trials comparing surgical approaches to hysterectomy for which well-validated instruments on pelvic organ function would need to be applied in a standardised manner [2]. In addition, postoperative recovery and quality of life should be regarded as key outcomes in trials on approaches to hysterectomy for benign disease as these are the ultimate tests of effectiveness. To date there is no study which has considered quality of life, pelvic organ function and cost-effectiveness for the three main types of hysterectomy. The aim of this study is to provide evidence on the optimal type of hysterectomy in terms of cost-effectiveness by way of a three-armed randomized controlled trial (RCT) between NDVH, TLH and TAH in a low-resource setting.

### Objectives

We hypothesize that TLH and NDVH are better than TAH in terms of time to recover, quality-adjusted life years (QALYs), pelvic organ function and cost-effectiveness. It will have the added advantage of providing valuable information on health-related quality of life, pelvic organ function and costing for the commonest gynaecological major surgical procedure.

#### Primary objectives

To find out the time to recover after surgery following TLH, NDVH and TAH.To calculate the total cost per surgery from a societal perspective for TLH, NDVH and TAH.To compare the cost-effectiveness of TLH versus NDVH versus TAH.

#### Secondary objectives

To determine quality of life following TLH, NDVH and TAH using QALYs.To evaluate the urinary, sexual and bowel function following hysterectomy.

## Methods

### Design, setting and participants

A multicentre three-armed (parallel groups) RCT was designed in accordance to the Consolidated Standards of Reporting Trials (CONSORT) recommendation for pragmatic trials [12]. The final report will follow the CONSORT 2010 guidelines as well as its extension to non-pharmacological interventions and pragmatic trials [13]. The Standard Protocol Items: Recommendations for Interventional Trials (SPIRIT) guidelines for reporting trial protocols were followed in writing this protocol (Additional file 1) [14].

The study is being done in the professorial gynaecology unit of the North Colombo Teaching Hospital, Ragama, Sri Lanka and the gynaecology unit of the District General Hospital, Mannar, Sri Lanka. Eligible participants are patients requiring hysterectomy for non-malignant uterine causes. Exclusion criteria are uterus > 14 weeks, previous pelvic surgery, those requiring incontinence surgery or pelvic floor surgery, any medical illness which caution/contraindicate laparoscopic surgery and patients who cannot read and write. Eligible patients will be aware that they will be randomly assigned to undergo one of the three procedures. The main exposure variables will be NDVH and TLH. The control group will consist of patients undergoing TAH (Fig. 1). Schedule of enrolment, interventions and assessments are shown in Fig. 2.

**Fig. 1 Fig1:**
[figure not shown]
Participant flow diagram. ^#^-The required numbers are for both study centres

**Fig. 2 Fig2:**
[figure not shown]
Schedule of enrolment, interventions and assessments. ^#^- preoperative assessment done 1-day prior to surgery. *-via postal assessment

### Outcome measures

The primary outcome is time to recover following hysterectomy (earliest time to resume all or a combination of activities done prior to surgery; resumption of cooking, washing clothes, sexual activity and occupation). The secondary outcomes are operative time (skin to skin), postoperative hospital stay, anaesthesia time, complications (bladder injury, ureteric injury, bowel injury, convert to laparotomy, vault haematoma, blood transfusion, postoperative fever, skin wound infection, urinary tract infection, respiratory tract infection, deep vein thrombosis/pulmonary embolism, re-operation), postoperative pain and total pain medication per day per patient, QALYs, urinary, sexual and bowel function and total cost per surgery. The outcome measures are shown in Table 1.

**Table 1 Tab1:** Outcome measures and study instruments

Outcomes	Study instrument
Time to recover	Patient filled data sheet at 6 weeks
Operative time	Data sheet on operative period filled by research assistant.
Postoperative hospital stay	Postoperative data sheet filled by research assistant
Cost	Direct costs based on preoperative, operative, postoperative, 6-week and 6-month data sheets filled by research assistant Indirect costs based on preoperative, postoperative, 6-week and 6-month data sheets filled by patient
Complications	Data sheet on operative, postoperative, 6-weeks and 6-months period filled by research assistant
Anaesthesia time	Data sheet on operative period filled by research assistant
Pain scores and pain medication	Data sheet on postoperative period filled by research assistant
Blood loss/change in haematocrit	Data sheet on operative and postoperative period filled by research assistant
QALYs	Paper-based EQ-5D-3L (Sinhala/Tamil) [16]
Urinary function	ICIQ-FLUTS (Sinhala/Tamil) questionnaire [18, 19]
Vaginal and sexual function	ICIQ-VS (Sinhala/Tamil) questionnaire [20]
Bowel function	Bowel symptoms questionnaire [21]

*EQ-5D-3L* EuroQoL group questionnaire on health-related quality of life, *ICIQ-FLUTS* International Consultation on Incontinence modular Questionnaire on Female Lower Urinary Tract Symptoms, *ICIQ-VS* International Consultation on Incontinence modular Questionnaire on Vaginal Symptoms, *QALYs* Quality-adjusted life years

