### Sample size calculation

The primary outcome is the time to recover following surgery. A difference of 7 days was considered a clinically significant difference based on time to recover following TAH (28.1 days, SD 9.5), VH (21.3 days, SD 8.5) and LAVH (19.7 days, SD 7.5 days) in a study published in the *BJOG* by Ottosen et al. [7]. Using the mean and SD of the above data, a type 1 error of 0.01 and a power of 80% with a loss to follow-up of 20% produces a sample size of 49 patients per arm (total of 147). The reason for a type 1 error of 0.01 (two-sided) was for a Bonferroni adjustment for multiplicity to keep the overall *p* value to less than 0.05 after pairwise comparisons.

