### Randomization

Block randomization in multiples of three will be carried out at each study site by opening sealed envelopes containing computer-generated block randomization numbers, with block sizes of six and nine to ensure roughly equal numbers of patients in each arm at any point in the study. The patients and medical team will not be blinded to the intervention with only the statistician performing the analyses being blinded.

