## Discussion

Studies in low-resource settings are hampered by financial limitations and feasibility in terms of time and collection of good quality accurate data. This protocol considers many relevant aspects concerned with the comparison of total abdominal, non-descent vaginal and total laparoscopic hysterectomy in one study for a lower-middle-income country where evidence on surgical outcomes especially in the form of randomized controlled trials are hard to come by. We believe these reasons make this protocol appealing for other researchers in similar settings.

As this is a multicentre study the involvement of multiple surgeons is inevitable and this can raise the issue of various skill levels and affect the outcome of surgery rather than a single operator. Although the issue of multiple surgeons is a limitation to the study itself, the generalisability of the results to the rest of the country would be more in our design of a pragmatic multicentre study involving multiple surgeons for each method rather than a single-centre study with a single surgeon for each method. In a study of this nature, it would not be possible to blind the patients nor the surgeons as the scars are distinct in each method. Although this is a limitation it is unavoidable and only the statistician will be blinded. The use of objective questionnaires, for patients’ as well as for assessors will also help to minimize bias [12].

The primary outcome, of time to resume usual activities, could be subject to recall bias. As it is a patient-reported outcome it has the advantage of being the best estimator of convalescence in the eyes of patients despite being subjective. Pelvic organ function is also assessed through patient-filled questionnaires as there is no objective method of assessing postoperative pelvic organ function. Although patient-reported outcomes can be subjective, validated questionnaires such as the ones used in this study make these assessments more valid and reliable. These questionnaires are the only available, non-invasive and generically applicable tools that can be used in low-resource settings.

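### The primary outcome is worded inconsistently (all usual activities, or all or a combination of four), so the recovery milestone is not fixed and can vary between women

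*Protocol article*

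**What the plan says.** - **Abstract, Methods:** the primary outcome is the "earliest time to resume all of the usual activities done prior to surgery". The set of activities is open and all of them must be resumed.
- **Outcome measures:** it is the "earliest time to resume all or a combination of activities done prior to surgery", followed by a list of four: "resumption of cooking, washing clothes, sexual activity and occupation".
- **Outcome measures, Table 1:** the instrument is a "Patient filled data sheet at 6 weeks".
- **Randomization:** "The patients and medical team will not be blinded to the intervention with only the statistician performing the analyses being blinded".
- **Sample size calculation:** "A difference of 7 days was considered a clinically significant difference", with planning values "TAH (28.1 days, SD 9.5), VH (21.3 days, SD 8.5) and LAVH (19.7 days, SD 7.5 days". The article does not say which definition of recovery lies behind these values.
- **Data analysis:** the end-point is called the actual time to recover, without further definition. Women not recovered at 6 weeks are followed further.
- **Discussion:** "The primary outcome, of time to resume usual activities, could be subject to recall bias". The outcome is also acknowledged to be subjective.
- **Economic evaluation:** time to recover is one of the two effect measures in the ICER.

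**The concern.** Resuming all activities names one milestone, the last activity to return. Resuming all or a combination, taken at the earliest time, can be met by a subset, and nothing says which subset or how large. The two sections also differ in the set of activities: open in the abstract, four named ones in Outcome measures.

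This variable sizes the trial, is the end-point of the Kaplan–Meier and Cox analyses, and feeds one ICER. Its definition also decides who counts as not yet recovered at 6 weeks. The woman supplies the answer herself, from memory and knowing her route of surgery. An open milestone therefore adds noise and leaves room for expectations about the route to influence which milestone is reported. Blinding the statistician does not repair that.

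**Working it through.** **1. The plan's own sample size.** Inputs from Sample size calculation: difference 7 days, SDs 9.5 (TAH) and 8.5 (VH), two-sided alpha 0.01, power 80%, loss 20%.

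- Pooled SD = √((9.5² + 8.5²)/2) = √81.25 = 9.014.
- n = 2 × 81.25 × (2.576 + 0.842)² / 7² = 38.7, so 39 evaluable per arm.
- 39 / 0.80 = 48.75, so 49 per arm and 147 in total.

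The stated figure is reproduced. The arithmetic is not in question.

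**2. How far apart the milestones could be (assumption only).** The article reports no times for single activities. Suppose four exchangeable normal components with common SD 8.5 days (borrowed from the VH planning value) and within-woman correlation ρ. The expected order statistics of four standard normals are ±1.029 and ±0.297, so:

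- last minus first = 2.059 × SD × √(1−ρ)
- last minus second = 1.326 × SD × √(1−ρ)
- last minus third = 0.732 × SD × √(1−ρ)

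| ρ | all four − first | all four − two of four | all four − three of four |
|---|---|---|---|
| 0 | 17.5 days | 11.3 | 6.2 |
| 0.5 | 12.4 | 8.0 | 4.4 |
| 0.8 | 7.8 | 5.0 | 2.8 |
| 0.9 | 5.5 | 3.6 | 2.0 |

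With SD from 7.5 to 9.5, last minus first is 10.9–13.8 days at ρ = 0.5 and 4.9–6.2 days at ρ = 0.9.

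**3. Effect on the arm difference if milestone choice differs by arm.** Bias = gap × difference between arms in the share using the looser milestone. At 39 per arm, SE = 9.014 × √(2/39) = 2.041 days. The false-positive rate at nominal 0.01 is P(Z > 2.576 − bias/SE); the other tail is negligible.

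- 10-day gap, 20 points: bias 2 days; 2.576 − 0.980 = 1.596; rate about 0.055.
- 10-day gap, 30 points: bias 3 days; 2.576 − 1.470 = 1.106; rate about 0.13.
- A 7-day bias needs something like a 14-day gap with a 50-point difference.

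**4. Effect if milestone choice is the same in every arm.** There is no bias under the null, but the variance grows. For a 50/50 mix, SD = √(81.25 + gap²/4), and power for a 7-day difference is P(Z < 7/SE − 2.576).

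| Gap | SD | Power at 39 per arm |
|---|---|---|
| none | 9.01 | 80% |
| 7 days | 9.67 | 73% |
| 10 days | 10.31 | 66% |
| 14 days | 11.41 | 55% |

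Steps 3 and 4 use the comparison of means behind the plan's sample size, as an approximation to the planned Cox comparison.

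**The case against.** The strongest reply is that the two wordings need not conflict. A combination may simply mean whichever of the four activities a given woman did before surgery; a woman without an occupation, for instance, would be judged on the rest. The list joins its items with *and*, which fits that reading. It is plausible, and it makes *incompatible* too strong a word. But both wordings already limit the activities to those done before surgery, so on this reading the extra phrase adds nothing, and the article nowhere says that this is meant. The ambiguity stands.

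Three stronger inferences are tempting, and the documents do not support them:

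- *The recovery time shifts by more than the 7-day target.* In the model above this holds for first-of-four when the correlation is below roughly 0.8 to 0.87. It fails for three of four even under independence (6.2 days). The model also gives each activity the SD of overall recovery after VH, which is a convenience and not evidence.
- *That shift can be set against the 7 days.* The 7 days is a difference between arms. A change of milestone that moves all arms alike is a change of level and leaves the contrast unbiased.
- *The 7 days and the SDs cannot hold under both definitions.* This is not shown. In the same model the first and last of four have equal SDs, and with the TAH and VH planning values the arm difference at ρ = 0.5 is 6.8 ± 1.029 × (9.5 − 8.5) × 0.707: 7.5 days for the last activity and 6.1 for the first.

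The full protocol, the analysis plan and the data sheets are not shown and may settle the rule. The article also discloses recall bias, subjectivity and lack of blinding. Disclosure does not supply the missing definition.

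**Conclusion.** The wording conflict is certain from the text. The primary outcome has a stricter and a looser wording, and no section of the article chooses between them. Followed as written, the Outcome measures section lets the milestone vary between women.

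The numerical consequence is conditional. If milestone choice differs by arm, a bias of a few days is conceivable, and 2 to 3 days would raise the nominal 0.01 error to about 0.055 to 0.13. If choice is alike across arms, the cost is power, down to roughly 73% to 55% for gaps of 7 to 14 days in an even mix. These figures rest on assumed component times, correlations and shares, none of which the documents give. The case for correction rests on the primary end-point lacking a fixed meaning, not on any one of these figures. A single definition does not by itself change the sample size: if the 7 days and the quoted SDs apply to it, 49 per arm stands.

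**What to change.** Use one definition in the abstract, Outcome measures, Data analysis and Discussion: days from surgery to the latest first-resumption date among those of the four listed activities that the woman did before surgery. Delete the words that admit a combination.

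To support it:

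- make sure the preoperative sheet records which of the four activities she did, and the 6-week sheet a day for each; add these items if they are absent (neither sheet is shown);
- derive the composite by program instead of asking for one overall date;
- report the component times as secondary outcomes;
- fix the rule before the arms are compared.

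The cost is a short clarification and, at most, a few added items on two sheets. Under the stricter rule a few more women will be unrecovered at 6 weeks and need the later follow-up that Data analysis already plans. Recruitment began on 1 August 2016, so component dates may not be recoverable for some women already enrolled. They should be sought where possible, and the number not recovered reported.

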### Patient selection and data collection

Eligible patients will be identified, counselled and enrolled by gynaecologists at each study centre. Before entry into the study the gynaecologist will explain to a potential patient the aims, methods, reasonably anticipated benefits and potential hazards of the study. Patient information sheets will be distributed to eligible patients and a research assistant will be available for a more detailed explanation. They will also explain to patients the potential benefit of extended long-term follow-up that would otherwise not be available and other intended benefits to the healthcare system as well as the country by participation in this research. After sufficient information, informed written consent will be obtained. Research assistants will assign enrolled participants to have either a TLH, NDVH or a TAH (Fig. 1). Patients who decline participation in the study will have standard treatment (TAH).

A preoperative questionnaire on general information, quality of life, pelvic organ function (urinary, vaginal and sexual and bowel function) and costs incurred up to surgery would be filled in by the patient while another on relevant medical information would be filled by a research assistant a day prior to surgery. Standard techniques of TLH, TAH and NDVH would be followed [15, 16]. The decision to convert to laparotomy at TLH or NDVH would be at the discretion of the primary surgeon.

Data on operative time, complications, instruments and medications used and staff allocation during surgery will be entered into a data collection sheet immediately after surgery. During the postoperative period the following information will be collected by a research assistant using a datasheet; complications, pain scores and analgesic medication and investigations. A patient-filled questionnaire will obtain costs incurred by the patient due to hospital admission. The health utility scores based on paper-based EuroQoL group health-related quality of life (EQ-5D-3L) questionnaires will be estimated on day 2 and 1 week post-surgery. (A self-addressed stamped envelope along with an EQ-5D-3L form will be provided to the patient on discharge with instructions to mail the 1-week assessment).

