### Compliance issues

Participants can exit the trial at any given point. Exit is defined as exiting the trial altogether or wanting another procedure different from the one allocated by randomization. If they exit after randomization but prior to surgery it will be mentioned but they will not be included in the analysis. However, if they wish to exit the trial after surgery, we will retain their data and their permission to access healthcare records unless consent for these activities is explicitly withdrawn. We will also actively try to minimize actual loss to follow-up by contacting patients through available contact information and access to information in hospital. We feel the rate of non-compliance will be low as well-motivated women will participate in a study of this nature. We also feel that it will be the same for participating gynaecologists as competent and well-motivated individuals who want to help answer the research question were chosen. Divergence from a pre-specified trial arm will be documented with reasons and included in the analysis of the originally allocated trial arm.

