### Data analysis

All randomized patients will be included in the analyses. A single principal analysis will be done comparing the three arms (TAH, NDVH and TLH) 12 months after the last woman has had her operation. The fact that the trial will be conducted at two centres will be taken into account during data analysis.

A Kaplan–Meier survival analysis will be done for the primary outcome which is time to recover following hysterectomy. The end-point is the actual time to recover. It will be assessed and documented at the 6-week clinic visit. Patients who have not recovered by 6-weeks will be followed-up beyond 6-weeks to detect complications and the actual time to recover. Post hoc pairwise analysis between TAH, NDVH and TLH will be done using COX regression.

Other outcomes that need follow-up; QALYs, urinary, vaginal and bowel functions will also be analysed using Kaplan Meier survival analyses. The end point for QALYs is 6-months while for urinary, vaginal and sexual function it is 1-year. Patients who do not complete follow-up in these secondary outcomes will be right censored up to their respective end-points. Post hoc pairwise analysis between TAH, NDVH and TLH will be done using COX regression. The other outcomes; operative time, anaesthesia time, postoperative hospital stay, cost, pain scores and blood loss will be analysed using Kruskal-Wallis test with post hoc comparisons. The complications will be described for each category. A fully specified Statistical Analysis Plan will be provided before opening the database.

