### Safety monitoring and premature termination of study

All surgeries will be done by consultants competent in the relevant type of hysterectomy, i.e., for an example all hysterectomies will be done by specialists who have operated on a minimum of 25 procedures. Any complication would be managed as per standard guidelines and necessary multidisciplinary input sought if required. All complications will be reviewed by an independent clinical review panel comprising three experienced gynaecologists. A list of all the possible complications will be made available at each site. It is the responsibility of the researchers and all other grades of staff to inform the clinical review committee of any complication through incident report forms, which are available in each setting. The clinical review panel will assess if the complications in the TLH or NDVH group exceed in amount or severity compared to the standard treatment (TAH group). If so, the disadvantaged arm of the study will be terminated.

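### The complication list names skin wound infection but no vaginal vault or pelvic infection, so operative-site infection is not recorded on a comparable basis across the three routes

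*Protocol article*

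**What the plan says.** The Outcome measures section of the protocol article makes complications a secondary outcome and defines them by a list in brackets. The infection-related part of that list sits within "vault haematoma, blood transfusion, postoperative fever, skin wound infection, urinary tract infection, respiratory tract infection". The other items are visceral injuries, conversion to laparotomy, thromboembolism and re-operation. The list has no item for infection of the vaginal vault or pelvis, and no open category. Table 1 has a research assistant record complications on the operative, postoperative, 6-week and 6-month data sheets.

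The Data analysis section plans description only: "The complications will be described for each category".

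Two provisions affect who can have a skin wound. Under Patient selection and data collection, "The decision to convert to laparotomy at TLH or NDVH would be at the discretion of the primary surgeon". Under Compliance issues, "Divergence from a pre-specified trial arm will be documented with reasons and included in the analysis of the originally allocated trial arm".

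Complications also feed the safety review: "The clinical review panel will assess if the complications in the TLH or NDVH group exceed in amount or severity compared to the standard treatment". An arm judged worse can be ended. The same section says of the sites: "A list of all the possible complications will be made available at each site". That list is not shown.

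**The concern.** The list divides infection by body site, so the choice of sites decides what the outcome table can show. The operative site it names, the skin wound, is absent in an NDVH completed vaginally. The operative site that all three routes share, the vault, has no infection item, although the authors had it in mind when they listed haematoma there.

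Infection is one of the complications on which a reader of a three-route trial will compare the arms. The planned table would offer a skin wound row that is close to empty for NDVH and no row for the vault. If vault infection differs between routes in either direction, the table cannot show it as infection. A later analysis plan cannot repair this, because an event type that was not recorded cannot be analysed.

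**Working it through.** **Which item can apply to which arm** (from the list under Outcome measures)

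| Item | TAH | TLH | NDVH, not converted | NDVH, converted |
|---|---|---|---|---|
| Skin wound infection | yes | yes | no abdominal wound | yes |
| Vault or pelvic infection | not listed | not listed | not listed | not listed |
| Fever, vault haematoma, re-operation | yes | yes | yes | yes |

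The last row catches some consequences of a vault infection, but not as infection. A vault infection without any of them leaves no trace in the listed items.

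**Arm size.** The Sample size calculation section states that "a power of 80% with a loss to follow-up of 20% produces a sample size of 49 patients per arm (total of 147"). With a 7-day difference, SDs of 9.5 (TAH) and 8.5 (vaginal) and two-sided alpha of 0.01:
- mean variance = (9.5² + 8.5²)/2 = 81.25
- n = 2 × (2.576 + 0.842)² × 81.25 / 7² ≈ 38.7, so 39 per arm
- 39/0.8 = 48.75, so 49 per arm.

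The stated figure reproduces. It rests on time to recover and is used here only as the number of women per arm.

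**What the table would record.** Let s be the risk of skin wound infection where there is an abdominal wound, v the risk of vault infection, and c the proportion of NDVH converted. With n = 49:
- TAH: true n(s + v_TAH), recorded n·s
- NDVH: true n(c·s + v_NDVH), recorded n·c·s
- true difference minus recorded difference (TAH minus NDVH) = n(v_TAH − v_NDVH).

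The conversion terms cancel. The recorded absolute difference is therefore wrong only by the difference in vault infection between the two routes.

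The documents give no value for s, v or c. Every rate below is an assumption for illustration, with c = 0.

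| s | v_TAH | v_NDVH | TAH recorded / true | NDVH recorded / true | Difference recorded / true |
|---|---|---|---|---|---|
| 2% | 2% | 2% | 0.98 / 1.96 | 0 / 0.98 | 0.98 / 0.98 |
| 5% | 5% | 5% | 2.45 / 4.90 | 0 / 2.45 | 2.45 / 2.45 |
| 5% | 2% | 8% | 2.45 / 3.43 | 0 / 3.92 | 2.45 / −0.49 |
| 5% | 8% | 2% | 2.45 / 6.37 | 0 / 0.98 | 2.45 / 5.39 |

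Rows 1 and 2: with equal vault rates the difference is right, although TAH records half of its operative-site infections and NDVH none. Row 3: if vault infection is more frequent after NDVH, the table shows an NDVH advantage where the truth is slightly the reverse. Row 4: if it is more frequent after TAH, the table understates the NDVH advantage. The recorded column is the same in rows 2 to 4, so the table cannot tell these situations apart.

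**Conversion.** With an assumed c of 5% and s of 5%, NDVH would record 49 × 0.05 × 0.05 ≈ 0.12 skin wound infections. The NDVH row is then nearly empty, but not empty by definition.

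**The case against.** The other side has four good arguments.

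**A zero for skin wound infection after NDVH is correct.** Having no abdominal wound is a genuine consequence of the route. A reader might infer that the list favours NDVH by construction. The documents do not support that. Vault infection is left out in every arm, and the recorded difference errs towards NDVH only if vault infection is more frequent there, which nothing in the protocol shows. Route-specific items are also normal in such a list: conversion to laparotomy cannot occur after TAH. This argument stands in full. It limits the point to comparability and does not remove it.

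**The safety panel is not confined to the list.** A reader might infer that an excess of infection after NDVH could never reach the panel. The Safety monitoring section says otherwise: staff are to report any complication on incident forms, the panel reviews all of them, and each site holds a fuller list. The 6-month visit also asks about any complication. A vault infection is reportable by these means. What remains concerns the outcome list and the table built from it.

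**The data sheets and the site list are not shown.** They may carry a vault infection item or an open field. If so, they differ from the stated outcome list and the two should be aligned.

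**No infection composite or test is planned.** That is true, so no formal inference is at risk. But when the result is a description by category, the categories are the result.

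A reader might also compute the chance that TAH shows at least one infection and NDVH none. For risks of 2%, 5% and 10%, 1 − (1 − p)^49 gives 63%, 92% and 99%. These figures put every TAH infection in the skin and allow no NDVH conversion. They are an extreme illustration and do not measure bias.

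**Conclusion.** The point holds in a limited form. The stated outcome list records operative-site infection at the skin wound only. The category table will therefore show part of it after TAH and TLH, almost none after NDVH, and no difference in vault infection as infection.

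The size cannot be taken from the documents. With assumed skin and vault risks of 2% to 5%, about 1 to 2.5 vault infections per arm of 49 would go unnamed, and about 4 at an assumed vault risk of 8%. Whether this misleads on the TAH–NDVH difference depends wholly on whether vault infection rates differ between routes, which is unknown. The direction is open.

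The conclusion rests on reading the list as the set of recorded categories. The unseen data sheets or site list could already fill the gap. This is a cheap improvement to a descriptive secondary outcome and has no bearing on the primary outcome or the sample size.

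**What to change.** In the Outcome measures list and on the existing complication data sheets, record one item, operative-site infection, with the site noted as abdominal wound or vaginal vault/pelvis. Describe the combined item by allocated arm. Keep skin wound infection as a sub-category, with a note that in the NDVH arm it can arise only after conversion. Use the same wording in the complication list held at the sites, so that the outcome table and the panel's review count the same events.

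The cost is one extra field on sheets already in use. Recruitment began in August 2016, so women already treated can be completed only as far as their records allow. The report should say for how many women the vault item was collected prospectively. The change concerns what is recorded and leaves clinical care untouched.
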